## Research methods/design

### Study design and participants

In a single-masked, longitudinal, randomized, parallel-controlled study design, eligible participants or legally authorized representative (if the participant is under mechanical ventilation) who provide informed consent to the principal investigator (PI) or assigned study coordinator are randomly assigned into a KD intervention group or an SD control group in a 1:1 ratio. Block randomization method with a block size of four is performed by the study statistician. A randomization list is generated, and the random assignments are placed into closed envelopes. All nurses performing blood draws, core facilities and research staff (technicians, students and trainees) analyzing the primary outcomes are blinded to group assignment. A Standard Protocol Items: Recommendations for Interventional Trials (SPIRIT) schedule is presented in Fig. 2 and the SPIRIT checklist is shown as Additional file 1. Outcome measures are performed at three time points: at baseline within 72 h of injury, before discharge from the acute care unit to the rehabilitation hospital, and at discharge from the rehabilitation hospital. Neurological examination via International Standards for Neurological Classification of SCI (ISNCSCI), commonly referred to as the American Spinal Injury Association Impairment Scale (AIS), electrical perception thresholds (EPTs) [23], functional examinations via the Spinal Cord Independence Measure (SCIM) [24, 25], resting energy expenditure (REE) and blood collection (for metabolic, targeted proteomics and safety outcomes) are performed within 72 h of injury, prior to starting enteral feeding (baseline measure). Following acute care, patients are transferred to the University of Alabama at Birmingham (UAB) Spain Rehabilitation Center (SRC) for inpatient rehabilitation care with an average length of stay of 20 days for patients with acute SCI. Accordingly, subsequent examinations are performed prior to transfer to the SRC (rehabilitation measure) and discharge from the SRC at week 5 (discharge measure). A summary of the data collection schedule for the outcomes is shown in Fig. 2, and the flow diagram for the overall study design is shown in Fig. 3.

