## Outcome measures and analysis

The primary outcomes are as follows: 1) safety via biomarkers of systemic inflammation (C-reactive protein), lipids (total cholesterol, high-density lipoprotein cholesterol, low-density lipoprotein cholesterol and triglycerides), sodium, liver enzymes (alanine aminotransferase, aspartate transaminase, alkaline phosphatase, albumin, bilirubin, total protein, nutritional ketosis (β-hydroxybutyrate) and glycemic status (fasting blood glucose and insulin)); 2) neurological recovery (AIS) motor and sensory scores and EPTs; 3) functional independence (SCIM); 4) microbiome composition; and 5) serum biomarkers (targeted proteomics).

In compliance with goals of the National Institute of Neurological Disorders and Stroke common data elements initiative, we are utilizing portions of the SCI common data elements that are expected to increase the efficiency and effectiveness of our clinical research study and diet intervention, increase data quality, and facilitate data sharing and comparisons across studies. For data analyses and results reporting, we adhere to the guidelines for reporting results using the international spinal cord core dataset [28].

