### Procedures to measure functional independence

The SCIM is used for measuring functional independence [24, 25] and is, at present, the only comprehensive rating scale that measures the ability of patients with SCI to perform everyday tasks according to their value for the patient. It requires no manual testing and the range of the total score is 0–100. Although one American Spinal Injury Association In-Step certified clinician performs all examinations, inter-rater reliability between the primary examiner and back-up examiners are assessed periodically as a quality assurance measure for consistency and a precautionary measure in the event that a back-up examiner might be required. Examiners are blinded to the diet assignment. Neurological examinations are routine both in the acute and inpatient care (in the SRC) facilities under the supervision of physiatrist.

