### Statistical analysis

Statistical analyses for neurological recovery will include comparisons of means of motor and sensory function, functional independence and serum measurements (e.g., glucose, insulin, alanine aminotransferase and aspartate transaminase) between the two groups, as well as comparisons within each group of the changes from baseline to rehabilitation to discharge (which should take approximately 5 weeks). Descriptive statistics, including measures of central tendency (sample mean, sample median) and dispersion (variance) will be calculated for each group. For safety outcomes, instead of comparing the two groups to the established standard safety values, we will compare circulating levels of proposed outcomes at the various time points among the two groups. If there are no significant group differences in these outcomes, we will conclude that the KD intervention is safe. We will also calculate 95% confidence intervals for the mean group differences for these outcomes as an additional check on safety and feasibility. The primary method of analysis will be analysis of covariance (ANCOVA), regressing the 5-week outcomes (safety, motor and sensory recovery, functional independence, and glycemic state) on the randomly assigned diet, baseline values of the measures, and other covariates such as age and sex. Repeated measures ANCOVA will also be used. Statistical assumptions will be assessed using box plots, residual plots and normal probability plots. Secondary analyses, accounting for all time points, will be conducted using mixed linear models, including repeated measures models. An appropriate structure for the covariance matrix (e.g., the unstructured covariance matrix) will be selected for these models using the final data. When a model term is statistically significant, the Tukey–Kramer multiple comparisons test will be used to determine which specific pair of means are significantly different. This method will allow us to compare changes over time (within-group changes) and differences between groups simultaneously. Covariates (e.g., length of enteral and solid feeding and length of stay in acute and rehabilitation care) will be accounted for in these analyses. Overall cross-sectional between-group comparisons, such as baseline comparisons used to examine pretest parameters, may be performed using the two-group *t* test, and overall within-group comparisons may be performed using the paired *t* test. If assumptions of normality of distribution for the above tests are not tenable, variables may be transformed prior to analysis, or appropriate nonparametric tests, such as the Wilcoxon rank-sum and signed-rank tests, may be used. Statistical tests will be two-sided and will be performed using a 5% significance level. Stratified analyses accounting for different injury levels will also be performed. These analyses will be specific to the distribution of data in each individual subgroup, which will minimize heterogeneity and allow us to analyze subgroups that may be more statistically homogenous and clinically relevant. SAS software, version 9.4 or later, will be used to conduct the statistical analyses. Multiple imputation methods will be used to address missing data for variables with moderate amounts of missing data (≥10%) and after examining whether data are missing completely at random, missing at random, or missing not at random. Missing data analysis will not be performed on variables with <10% missing data to avoid statistical bias larger than that obtained through the use of complete case analysis.

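### SCIM model: the 72-hour SCIM baseline may predict 5-week SCIM only weakly, and the baseline motor score from the same visit, which could add precision, is not named as a covariate

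*Protocol article*

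**What the plan says.** The Protocol article, Outcome measures and analysis, lists functional independence by SCIM as the third of five groups of primary outcomes. Procedures to measure functional independence says that the scale "measures the ability of patients with SCI to perform everyday tasks according to their value for the patient" and that "the range of the total score is 0–100".

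Study design and participants puts the ISNCSCI examination and "functional examinations via the Spinal Cord Independence Measure (SCIM") in one battery of examinations, which "are performed within 72 h of injury, prior to starting enteral feeding (baseline measure"). Participants are in acute care with AIS grades A to C and injury levels C5 to T12. The same section provides for consent by a representative when a participant is ventilated.

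Statistical analysis sets one covariate rule for all the 5-week outcomes: "regressing the 5-week outcomes (safety, motor and sensory recovery, functional independence, and glycemic state) on the randomly assigned diet, baseline values of the measures". It then adds other covariates, with age and sex as examples. For the models using all time points it names time on enteral and solid feeding and length of stay, which are determined after randomization. Injury level appears only in stratified analyses. Baseline motor score and AIS grade are not named as covariates for SCIM.

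Randomization and blinding describes blocks of four and states no stratification factor.

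**The concern.** Adjusting for the baseline of the same measure pays off when that baseline predicts the outcome. SCIM rates independence in everyday tasks. Training in transfers, wheelchair skills, bowel and bladder management and daily living belongs to inpatient rehabilitation (Inpatient rehabilitation care), which follows acute care. In the first 72 h after a grade A to C injury a patient has little opportunity to show independence, whatever the later capacity. Baseline SCIM scores may then bunch together, and adjusting for them would remove little outcome variance.

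The motor score is examined at the same visit, can vary widely across C5 to T12, and is a plausible predictor of later independence. If it is left out, the SCIM comparison could run close to the precision of an unadjusted t test in a trial expecting 48 completers. Without stratification, a chance imbalance in motor function between the arms would also go largely uncorrected in the SCIM estimate.

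**Working it through.** **Inputs from the Protocol article (Power calculations; Abstract).** 24 per arm (60 enrolled, 80% completing), two-sided 5%, 80% power, SD 23.5 for motor score and 33 for light touch. No SD, detectable difference or correlation is given for SCIM, so SCIM results below are in SD units.

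**Step 1: reproduce the plan's figures.** Two-sample t test, noncentrality = difference / (SD × √(2/24)), 46 df.
- Motor: 19.5 / (23.5 × 0.2887) = 2.874, power 80.3%.
- Light touch: 27.3 / (33 × 0.2887) = 2.866, power 80.1%.

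Both agree with the stated 80%. The unadjusted detectable difference is 0.826 SD.

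**Step 2: baseline SCIM as the only covariate.** Residual SD = SD × √(1 − r²), 45 df. Each r is an assumed correlation between baseline and 5-week SCIM.

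| r | Variance removed | Detectable difference | Power at 0.826 SD |
|---|---|---|---|
| 0.1 | 1% | 0.822 SD | 80.4% |
| 0.2 | 4% | 0.810 SD | 81.5% |
| 0.3 | 9% | 0.788 SD | 83.5% |

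**Step 3: add the baseline motor score.** With s and m the correlations of baseline SCIM and baseline motor score with 5-week SCIM, and c their correlation with each other, R² = (s² + m² − 2smc) / (1 − c²). Residual SD = SD × √(1 − R²), 44 df. All three are assumed.

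| s | m | c | R² | Detectable difference | Power at 0.826 SD |
|---|---|---|---|---|---|
| 0.1 | 0.5 | 0.1 | 0.253 | 0.715 SD | 89.9% |
| 0.2 | 0.6 | 0.3 | 0.360 | 0.661 SD | 93.8% |
| 0.3 | 0.7 | 0.1 | 0.543 | 0.559 SD | 98.5% |

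First and last rows: the ends of the range over s 0.1 to 0.3, m 0.5 to 0.7, c 0.1 to 0.3. In the middle row, residual variance relative to baseline SCIM alone at r = 0.2 is 0.64 / 0.96 = 0.67. That is worth about 1 / 0.67 = 1.5 times the patients for this outcome.

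**Step 4: if the premise is wrong.** Suppose baseline SCIM correlates 0.5 with the outcome. Alone it removes 25% of the variance and gives 0.716 SD. Adding a motor score with m = 0.6 and c = 0.5 gives R² = (0.25 + 0.36 − 0.30) / 0.75 = 0.413 and 0.633 SD. The improvement is then 0.716 − 0.633 = 0.083 SD, against 0.810 − 0.661 = 0.149 SD in the middle case.

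**Step 5: chance imbalance.** If 23.5 is taken as the baseline motor SD (an assumption, since the article does not say at which visit it applies), the difference between arm means has a standard error of 23.5 × √(2/24) = 6.8 points. Under a normal approximation about one trial in three (31.7%) would start more than 6.8 points apart.

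Age and sex are left out of these figures. They use a few degrees of freedom, and their predictive value is unknown.

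**The case against.** The strongest reply is that nothing here is wrong. The covariate list is open, age and sex are only examples, and one sentence serves several outcome types. The exact list for each endpoint is ordinary analysis-plan content, and the full protocol and analysis plan are not shown. This stands against inferring that the motor score is excluded or will not be used: the article only does not name it. What remains is a suggestion to fix a useful covariate that is already collected.

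A reader might also infer that nearly every patient starts at the floor of SCIM, so that adjusting for it gains almost nothing. The article does not support that. It reports no baseline mean, SD, share at the floor or correlation, it mentions ventilation only in connection with consent, and eligibility from C5 to T12 could spread the scores. Compression is plausible, not shown.

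It is also true that ANCOVA with a weak covariate remains unbiased under randomization, and that the stated power figures are unadjusted and do not concern SCIM, so no stated figure is undermined. Baseline motor examinations and planned baseline comparisons would reveal unequal starting motor function. They would not, however, adjust the SCIM estimate for it. The analyses by injury level are described as subgroup analyses, so they do not clearly add precision to the overall comparison.

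**Conclusion.** The point holds as a matter of precision, not validity. For a primary outcome whose baseline is taken at a time when it may carry little information, the article names the same-measure baseline and an open list. It does not name a likely better predictor from the same visit.

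If baseline SCIM correlates 0.1 to 0.3 with 5-week SCIM, adjusting for it moves the detectable difference only from 0.83 to between 0.82 and 0.79 SD. Adding a motor score that correlates 0.5 to 0.7 brings it to about 0.72 to 0.56 SD. All of these correlations are assumptions, and the gain is smaller if baseline SCIM itself correlates 0.5 or more. The documents do not support reading this as bias, as a demonstrated floor effect, or as exclusion of the motor score.

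**What to change.** In Statistical analysis, or in the analysis plan if it does not already say so, prespecify the baseline ISNCSCI total motor score as a covariate in the SCIM ANCOVA and in the SCIM mixed model. It should be in addition to baseline SCIM, not in place of it: the planned within-group changes and the models over all time points still need the SCIM baseline, and it may prove more informative than assumed here. The choice should be fixed before outcome data are examined by group.

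The cost is one line of text and one degree of freedom, with no new data. If the motor score turns out to predict poorly, the loss is about that one degree of freedom.

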### Minimally acceptable intervention adherence rates

Adherence to diet will be closely monitored by the study team by measuring serum β-hydroxybutyrate levels once a week. A blood concentration of 0.5–3 mM (nutritional ketosis) will be considered safe and acceptable. Adherence will also be assessed using food records. The food record will be a simple checklist to indicate that supplied foods were consumed, with space to add the quantity of consumption and any deviations from the protocol. In addition, the study dietician will communicate directly with each participant at least weekly to improve adherence.

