### Randomization and blinding

Randomization is performed using the block randomization method, with a block size of four (study statistician). A randomization list is generated, and the random assignments placed into closed envelopes. Each study participant opens one of these envelopes to learn of their group assignment. Study patients will inevitably know their group assignment as we are limited by the difficulties of inadequate masking of the ketogenic diet, which is very restrictive and requires avoidance of usual foods like bread, pasta, rice, potatoes and a wide variety of fruits. In order to avoid a potential placebo effect or a participant biasing results due to knowledge of their diet, during the consenting process we simply explain that the study is designed to examine the impact of KD and SD on outcomes. In addition, individuals performing clinical and laboratory tests and the study statistician were blinded to the study interventions.

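### Safety is judged by randomised diet and non-significance is read as safe, so KD patients who have stopped the diet pull the result towards safe; no supporting on-diet comparison is described

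*Protocol article*

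**What the plan says.** In the Protocol article, Statistical analysis, the primary method is ANCOVA, "regressing the 5-week outcomes (safety, motor and sensory recovery, functional independence, and glycemic state) on the randomly assigned diet", with baseline values and covariates such as age and sex. For safety the section adds that "we will compare circulating levels of proposed outcomes at the various time points among the two groups". The decision rule follows: "If there are no significant group differences in these outcomes, we will conclude that the KD intervention is safe". There is a further step, "We will also calculate 95% confidence intervals for the mean group differences for these outcomes as an additional check on safety and feasibility", but no limit is given against which to judge the intervals. Mixed models are also planned: "Secondary analyses, accounting for all time points, will be conducted using mixed linear models, including repeated measures models". All of these compare the groups as randomised.

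Adherence is tracked. Under Minimally acceptable intervention adherence rates, β-hydroxybutyrate is measured and "The food record will be a simple checklist to indicate that supplied foods were consumed", with room for quantities and deviations. Despite its title, that section states no minimum rate. No safety analysis in Statistical analysis uses these records. Randomization and blinding describes the KD as a diet "which is very restrictive and requires avoidance of usual foods like bread, pasta, rice, potatoes" and a wide variety of fruits.

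**The concern.** For efficacy, analysis by randomised diet is cautious: non-adherence shrinks the difference and works against the claim. For safety the desired result is no difference, so the same shrinkage works for the claim.

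Examinations run to discharge from rehabilitation at about week 5 (Study design and participants). A KD participant who has returned to ordinary food can therefore still be sampled, and that value would count in the KD mean. For lipids, liver markers or sodium, the estimate would then understate what the diet does to patients who eat it.

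This is distinct from reading non-significance as safety. Replacing the test with a confidence interval and a margin would leave the estimate itself displaced towards zero. It also arises with complete data. Safety is the first of the listed primary outcomes and the first stated purpose of the trial.

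**Working it through.** **The plan's own figure first.** Power calculations gives 24 per group, SD 23.5 (motor) and 33 (light touch), and 80% power for differences of 19.5 and 27.3. The test settings are as planned: "Statistical tests will be two-sided and will be performed using a 5% significance level". The standardised differences are 19.5/23.5 = 0.830 and 27.3/33 = 0.827. A noncentral t calculation with 46 degrees of freedom gives power 0.803 and 0.801, so the stated 80% reproduces. No power is stated for any safety marker.

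**Inputs for the illustration**
- From the document: 24 per arm, two-sided 5% test.
- Assumed: true on-diet shift D = 0.8 SD; k of 24 KD participants off diet when sampled, with k = 0, 5, 7 or 10; off-diet values fully reverted (zero shift); k unrelated to the marker.

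**Step 1: size of the estimate.** The expected group difference is D × (24 − k)/24.
- k = 0: 0.80 SD
- k = 5: 0.8 × 19/24 = 0.63 SD
- k = 7: 0.8 × 17/24 = 0.57 SD
- k = 10: 0.8 × 14/24 = 0.47 SD

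The 95% interval half-width is about 2.013 × √(2/24) = 0.58 SD. With 7 off diet, an interval centred at its expected value already includes zero (0.57 − 0.58 < 0). The planned intervals are displaced together with the test.

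**Step 2: chance of a non-significant result.** These come from simulated two-sample t tests, where a miss is p ≥ 0.05.

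| Off diet (of 24) | Randomised comparison, D = 0.8 | On-diet KD only, D = 0.8 | Randomised comparison, D = 1.0 |
|---|---|---|---|
| 0 | 22% | 22% | 8% |
| 5 | 45% | 28% | 26% |
| 7 | 54% | 31% | 37% |
| 10 | 68% | 36% | 54% |

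The on-diet column drops the k stoppers and compares 24 − k KD participants with 24 controls.

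**Step 3: sensitivity.**
- Baseline adjustment (assumed correlation 0.5, D = 0.8): misses are 12%, 33%, 43% and 59%. The level is lower but the pattern is the same.
- Half reversion instead of full (stoppers keep 0.4 SD, unadjusted): the expected difference is 0.8 × (24 − k/2)/24 = 0.80, 0.72, 0.68 and 0.63 SD, and simulated misses are 22%, about 32%, 37% and 43%.
- Smaller harm with full adherence: a 0.5 SD shift is missed 60% of the time, so the non-significance rule is the larger weakness and dilution adds to it.

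**The case against.** Several objections have force.

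- **Time points.** A reader might infer that the safety conclusion rests on week-5 values alone. It does not. The safety comparison covers the various time points, including the sample before transfer to rehabilitation, and mixed models use all of them. Harm present before a later switch of diet could be seen. Those comparisons are still by randomised group, so dilution is reduced but not removed.
- **Who stays in the data.** A reader might take it as stated that diet-stoppers remain in the week-5 analysis. That is an inference from the grouping by randomised diet. The Abstract expects 80% completion (48 of 60), and some stoppers may be among the non-completers. Since 24 per arm is the completer number, the off-diet counts above would have to come on top of that loss.
- **No adherence figure.** Calling the diet restrictive explains why masking fails; it does not estimate adherence. Inpatient care, supplied meals or enteral formula, and dietician contact at least weekly all favour adherence.
- **Analysis by randomised diet is not an error**, and analysis sets are commonly left to a fuller document. What remains is not a missing detail: the article states a conclusion rule which, applied as written, turns non-adherence into evidence of safety.
- **Tolerability.** A reader might infer that a badly tolerated diet would look safer overall. The documents do not support that, because adverse events are recorded and reviewed separately. The point concerns the biomarker conclusion only.

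**Conclusion.** The point holds in a limited form. Comparing safety markers by randomised diet and concluding safe when no significant difference appears lets non-adherence favour that conclusion. No described safety analysis uses the adherence data to check this.

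The direction follows for any marker that moves back towards control values once the diet is stopped. The size is not known. Under the assumptions stated (0.8 SD on-diet shift, 24 per arm, 5 to 10 of 24 off diet, full reversion), the miss rate rises from 22% to between 45% and 68%. With half reversion it rises to between about 32% and 43%. With nobody off diet there is no dilution. The randomised comparison should stay; the weakness is letting it carry the safety conclusion alone.

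**What to change.** 1. Keep the comparison by randomised diet.
2. Add a supporting on-diet safety comparison at each scheduled time point: KD participants on diet at that visit against standard-diet participants at the same visit. Define on-diet status in advance from food records and ketone data.
3. Do not carry earlier samples forward for those who stopped. That would set early post-injury values against later control values and confuse diet with time since injury.
4. Leave β-hydroxybutyrate out as an outcome of this comparison, since it helps to define the group although it is listed among the safety markers.
5. Report days on diet, and state that safe will not be concluded from the randomised comparison alone.
6. First reconcile the ketone sampling frequency: once a week under Minimally acceptable intervention adherence rates, three times a week under Clinical procedures to measure safety.

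The cost is one further analysis set from data the trial already plans to collect. The on-diet comparison has fewer patients and is not protected by randomisation. If patients stop because a marker worsens, it can understate harm too. It should therefore be labelled as supporting and shown beside the randomised result, not in its place.

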**Fig. 2 Fig2:**
[figure not shown]
Standard Protocol Items: Recommendations for Interventional Trials (SPIRIT) schedule. *Allocation and baseline testing occur within 72 h of injury; postintervention assessments are performed prior to each patient’s discharge. ^¥^Including cholesterol, triglycerides, high-density lipoprotein cholesterol and calculated low-density lipoprotein cholesterol. ^&^As reflected by liver enzymes, alanine aminotransferase, aspartate transaminase, alkaline phosphatase, albumin, bilirubin and total protein. ^$^Serum fibrinogen, extracellular signal-regulated kinase 1/2, CD11b/CD18 integrin receptor, epidermal growth factor and receptor levels. AIS American Spinal Injury Association Impairment Scale, Wk week

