### Inpatient rehabilitation care

Patients in both groups undergo an intensive rehabilitation program for about 5 weeks. Therapy is offered 5 days (a total of 15 h) per week. The standard of care for both groups includes: respiration therapy, bed mobility, transfers, wheelchair mobility skills, bowel and bladder management, tone and spasticity management, and skills for performing other activities of daily living. Rehabilitation protocols and treatment hours are recorded for each patient. The average duration of stay in the SRC is 30 days for individuals with tetraplegia (injury level C4–C7) and 21 days for individuals with paraplegia (injury level T1–S5).

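### Feeding duration and length of stay arise after randomisation; between-group contrasts adjusted for them need not estimate the effect of assignment to the ketogenic diet and can be biased

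*Protocol article*

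**What the plan says.** All references are to the protocol article.

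- **Primary model (Statistical analysis).** An ANCOVA regresses the 5-week outcomes "on the randomly assigned diet, baseline values of the measures, and other covariates such as age and sex". The list is illustrative, not closed.
- **Secondary models (same section).** "Secondary analyses, accounting for all time points, will be conducted using mixed linear models, including repeated measures models". The choice of covariance structure and the Tukey–Kramer comparisons follow, and the text says this approach handles within-group change and between-group differences together.
- **Covariates (the next sentence).** "Covariates (e.g., length of enteral and solid feeding and length of stay in acute and rehabilitation care) will be accounted for in these analyses".
- **Timing (Fig. 2 legend).** "Allocation and baseline testing occur within 72 h of injury". Study design and participants adds that baseline measures are taken before enteral feeding begins, and that the last examination coincides with leaving the rehabilitation centre.

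The article describes no version of these models without the durations, and states no mediation aim that would call for them.

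**The concern.** Randomisation protects a comparison adjusted for characteristics fixed before assignment. It does not protect one adjusted for something that happens afterwards and that treatment may influence. Time on tube or solid feeding, and days in acute and rehabilitation care, are of the second kind.

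The trial's own hypothesis is that KD improves motor function and functional independence. If it does, patients on KD might reach oral feeding or discharge at different times. Holding the durations equal across arms could then remove part of a real effect. It could also produce an apparent effect where there is none, because a duration may share unmeasured causes with the outcome.

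At stake is the meaning of the diet estimates from the models that use all time points. The plan also intends to conclude that KD is safe when no significant group difference is seen. If the same adjusted models serve that purpose, an adjustment that shrinks a true difference favours that conclusion.

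**Working it through.** **1. Are the covariates post-randomisation?** Allocation is within 72 h of injury, and baseline precedes enteral feeding, so the feeding durations accrue after baseline. Acute stay begins at admission, but its length is fixed only when the patient leaves; rehabilitation stay lies wholly later. The Interventions/groups section makes oral meals depend on ability to swallow or to take liquid or solid feeding. None of the four durations is known at assignment.

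**2. The plan's own figure.** Power calculations gives 24 per group, motor SD 23.5, difference 19.5, two-sided 5%, 80% power. Standard error = 23.5 × √(2/24) = 6.78; noncentrality = 19.5/6.78 = 2.87 on 46 degrees of freedom; power = 80.3%. The figure reproduces, so 19.5 and 23.5 are used below as a scale.

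**3. Duration sharing a cause with the outcome.** Let T be diet, U an unmeasured recovery factor (SD 1), and M a duration with within-arm SD 1.

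- Outcome: Y = τT + gU + error
- Duration: M = aT + cU + error
- Regressing Y on T and M gives a coefficient c·g for M, and a coefficient τ − a·c·g for T. The bias is therefore −a·c·g.

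The document gives none of a, c or g. Assume g = 0.7 × 23.5 = 16.45 motor points.

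| Shift a (SD) | c | Bias −a·c·g (points) | Power for 19.5, adjusted | Type I error, adjusted |
|---|---|---|---|---|
| 0 | −0.5 | 0 | 84% | 5% |
| −0.3 | −0.3 | −1.5 | not run | not run |
| −0.5 | −0.5 | −4.1 | 62% | 9% |
| −0.8 | −0.7 | −9.2 | 35% | 29% |
| +0.5 | −0.5 | +4.1 | not run | not run |

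Power and type I error were simulated at 24 per arm with a single outcome time. Without the duration in the model, power was about 80% and type I error about 5% throughout. The last row shows the sign reversing when diet lengthens the duration instead of shortening it.

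**4. Duration driven by the outcome itself.** If M = −kY + error, the diet coefficient becomes δ(1 − r²), where r is the within-arm correlation of duration and outcome. For δ = 19.5:

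- |r| = 0.3: 19.5 × 0.91 = 17.7
- |r| = 0.5: 19.5 × 0.75 = 14.6
- |r| = 0.6: 19.5 × 0.64 = 12.5

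Here a true null stays null, because diet then does not move the duration.

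**5. Which mixed-model contrasts move?** Steps 3 and 4 concern one outcome time. Now take baseline as one of the outcome times, a separate mean for every arm and time, complete data, and one duration value L per patient entered as a main effect with slope β. The adjusted mean in arm g at time t is Ȳ(g,t) − β·L̄(g).

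- Between-arm difference at discharge: the raw difference minus β·(L̄(KD) − L̄(SD)). It moves whenever β is not zero and mean durations differ between arms.
- Between-arm difference in change from baseline: the term β·(L̄(KD) − L̄(SD)) appears at both times and cancels. This contrast does not move.

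A numerical check with an unstructured covariance agreed. The change contrast was the same with and without stay (18.58 and 18.58 in one run), while a discharge contrast moved from 21.4 to 18.3. The cancellation is not guaranteed if baseline is a covariate, if the duration is crossed with time, or if data are incomplete. The article does not say which form will be fitted.

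**The case against.** **Only secondary models are affected.** The covariate sentence follows the description of the mixed models, so that is its most direct reference. A reader might infer that the primary ANCOVA is adjusted for the durations too. The text does not establish this: it names baseline value, age and sex. Nor does it rule it out, since the list is open and Power calculations describes the primary analyses as making between-group and within-group comparisons simultaneously, close to the wording used for the mixed models. The objection stands as a limit on scope.

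**Bias is not shown.** No passage says that diet changes these durations. The article links rehabilitation stay to injury level, which is fixed before assignment: "The average duration of stay in the SRC is 30 days for individuals with tetraplegia", against 21 for paraplegia. A reader might infer that the diet effect is biased; the document supports only that it can be. This stands too.

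**The change contrast may be untouched.** Correct under the conditions in step 5, so the figures in steps 3 and 4 cannot be carried over to every mixed-model estimate.

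**The adjustment may be meant to allow for variable assessment time**, since the last visit is tied to discharge. That is a reasonable aim, but discharge timing can itself respond to recovery, so conditioning on it does not restore the randomised comparison.

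**Neighbouring points that do not carry this one.** A reader might add that AIS grade and injury level are not named as covariates. The list is open and analyses stratified by injury level are planned, so this is detail an article may omit. The article's differing average rehabilitation stays are a separate descriptive mismatch.

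**Conclusion.** The point holds in limited form. The plan commits to adjusting for variables that arise after randomisation, most directly in the secondary mixed and repeated measures models, and does not exclude them from the primary ANCOVA. Between-group contrasts adjusted in this way need not estimate the effect of assignment to KD and can be biased in either direction.

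Neither size nor sign can be derived from the document. The bias is zero if diet does not affect the durations. With shifts of 0 to 0.8 SD and correlations of 0.3 to 0.7 in absolute value it reaches about 9 motor points, but these inputs and the value of g are assumptions, and 19.5 is the plan's detectable difference, not an expected effect. A reader might take the fall from 19.5 to 12.5 as the loss to expect from the mixed models. That does not follow, because it comes from a single-time regression with an assumed correlation, and a change-from-baseline contrast may not move at all.

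**What to change.** In Statistical analysis, replace the covariate sentence with one stating that every model estimating the diet effect, primary or secondary, adjusts only for variables measured before randomisation: baseline score, age, sex and, if wanted, baseline injury level and AIS grade. Remove length of enteral and solid feeding and length of acute and rehabilitation stay from those models. Report them by arm as descriptive outcomes, or use them in an analysis labelled exploratory and not presented as the effect of assignment.

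The change is to wording only; no visit or data item changes. The downside is that outcome variation explained by the durations is no longer removed. In the one simulated case where diet left stay unchanged (c = −0.5, g = 16.45), dropping the covariate lowered power for 19.5 points from about 84% to about 80%, the level the plan was sized for.
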